### 13.1.3 Exploratory Analyses

Exploratory endpoints shall include the pH analyses, symptoms such as itching, irritation, and general vaginal discomfort (as well as other symptoms), microbiota analysis, microarray analysis, and multiplex immunological analysis.

#### 13.1.3.1 Additional Nugent Score Analyses

Change in Nugent Score from baseline (no treatment phase) through the treatment phases and follow-up will be summarized and compared between the test articles.

#### 13.1.3.2 pH Analysis

Change in pH measurement from baseline (no treatment phase) through the treatment phases and follow-up will be summarized and compared between the test articles.

#### 13.1.3.3 Symptom Analysis

Diary questionnaire information from baseline (no treatment phase) through the treatment phases and follow-up will be summarized and compared between the test articles.

#### 13.1.3.4 Microbiota Analysis

Abundance values will be defined as operational taxonomic units (OTUs). In order to compare microflora diversity, Shannon's diversity index will be calculated for each subject at each treatment phase as the abundance values using OTUs. The Shannon's diversity index ( $S$ ) is

defined as 
$$S = - \sum_{i=1}^{119} p_i \log(p_i)$$
 where  $p_i$  denotes the proportional abundance values at the  $i$ th OTU. The lactobacillus ratio will be calculated for each subject at each treatment phase, as the ratio of total abundance value for the lactobacillus OTUs to the total abundance value for all the OTUs.

To determine if the linear trends in the  $S$  and lactobacillus ratio trajectories differ significantly across subjects and treatment phases, the following linear mixed effect model will be applied to the data  $Y_{it} = \mu + a_i + b_i t + \epsilon_{it}$ . The fixed effect being the intercept only and random effects being subject intercepts and slopes where  $Y_{it}$  denoted the  $S$  value of subject  $i$  at time point  $t$  and  $\mu$  is an unknown fixed constant,  $a_i$  is a random subject intercept,  $b_i$  a random subject slope, and  $a_i$ ,  $b_i$ ,  $\epsilon_{it}$  are independent normal random variables.

In order to determine if a statistical relationship existed between microbial diversity and vaginal symptoms, a weighted least squares analysis will be applied to the data. Severity of vaginal symptoms will be treated as ordinal values 0, 1, 2, and 3, for example. The weighted least

squares model  $\bar{Y}_{id} = \mu_0 + \mu_1 d + \epsilon_{id}$  will be used to test the linear effect of vaginal symptoms with respect to microbial diversity. Where  $\bar{Y}_{id}$  denotes the average  $S$  of subject  $i$  at dryness  $d$ . The quantities  $\mu_0$  and  $\mu_1 d$  are constants representing intercept and slope respectively.

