| Dosage, Dose Form, and Route of Administration: | 
L. rhamnosus GR-1® and L. reuteri RC-14® in preparations consisting of freeze-dried bacteria capsules containing <math>2.5 \times 10^9</math> CFU of each of GR-1® and RC-14® (at time of manufacture).
 
The INHP will be administered vaginally two (2) times daily for three (3) consecutive days.
                                                                                                                                                                                                                                                                                                                                                                                                                                                                                                                                                                                                                                                                                                                                                                                                                                                                                                                                                                                                                                                                                                                                                                                                                                                                                                                                                                                                                                                                                                                                                                                                                                                                       |

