| Study Design:                                   | 
This is a prospective, randomized, double-blind crossover study.
 
Fourteen (14) post-menopausal women with a Nugent Score of four (4) to six (6) will be included in the study.
 
Subjects will undergo the following treatment phases:
 
 
• Two weeks of no treatment (Days 1-15); followed by
 
• Three days in which each subject randomly receives either two intravaginal placebo capsules or two intravaginal probiotic capsules (Days 16-18) per day; followed by
 
• 18 day wash-out period; followed by
 
• Three days in which each subject randomly receives either two intravaginal placebo capsules or two intravaginal probiotic capsules (Days 37-39) per day.
 
 
The capsules given on Days 37-39 will not be the same as the capsules given on Days 16-18. During one treatment period the probiotic will be given and during the other treatment period, placebo will be given.
 
Both the subjects and the investigator will be blinded as to placebo and probiotic treatments. Subjects will provide vaginal samples on Days 1, 5, 15, 19, 26, 36, 40, and 47. An additional sample may be taken on Day 129 if the subject is still colonized at Day 47.
 
A diary to track compliance and to rate general vaginal discomfort and other adverse events will be given to the subjects on Day 1, Day 15 and Day 36 to be reviewed by the study Investigator or designee at the following visit.
 
Subjects that remain colonized with the probiotic strains at Day 47 will be queried monthly via telephone to monitor for adverse events and have a follow-up visit on Day 129 where a vaginal swab will be taken to determine if they are still colonized by the probiotic strains.
 
Subjects that are not colonized with the probiotic strains at Day 47 will be queried monthly via telephone for adverse events until Day 129. No visit is required at Day 129.
 |

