#### 5.3.2.2 Clinical Benefits of Probiotics

A number of clinical trials have investigated the use of probiotics or candidate probiotics for the treatment of BV. These are summarized in a recent review by MacPhee et al. Cure rates in women receiving probiotics delivered intravaginally typically exceeded 50% and reached as high as 100% in one trial. Rossi et al. assessed qualitatively the effectiveness of *L. rhamnosus* at normalizing vaginal pH and improving BV symptoms. Participants reported decreases in itching, vaginal discharge and burning at the 12-month and 24-month follow-up visits.

Probiotics administered for urogenital health in general, have been well-tolerated. Side-effects from probiotic treatment, although rare, have occurred and included bacteria in the blood,

inflammation in the lining of the heart and localized infections that were possibly linked to heavy consumption of dairy products.

Lactobacilli, including the species *L. rhamnosus* and *L. reuteri* are normal inhabitants of the gastrointestinal (GI) and urogenital tracts, and as such, *Lactobacillus rhamnosus* GR-1® (GR-1®) and *Lactobacillus reuteri* RC-14® (RC-14®) were recovered from the healthy urethra and vagina, respectively. The intended indication for this product is to maintain a healthy vaginal microbiota and thereby prevent vaginal infections such as BV and VVC. Studies investigating use of GR-1® and RC-14® in prevention of BV in women without symptoms of BV have suggested that, GR-1® and RC-14® can prevent development of BV (as defined by high or intermediate Nugent Scores) and reduce Nugent Scores.

Studies investigating transient colonization of GR-1® and RC-14® in the GI and vaginal tracts have shown that detection of GR-1® and RC-14® (after oral and after vaginal application) declines gradually with time and that the strains cannot be detected 30 days after cessation of oral administration.

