#### **Visit 4 – Day 19 (+1 day)**

Subjects will return to the clinic four (4) days after Visit 3. The following assessments will be performed:

- Subject diaries will be reviewed and subjects queried regarding any adverse events they may have experienced;
- A vaginal health questionnaire will be completed;
- Five (5) vaginal samples and a vaginal pH measurement will be taken in the same manner as described for Visit 2;
- Subjects' diaries will be returned to the subjects to rate general vaginal discomfort and record any other adverse events daily until their next visit;
- Review concomitant medications; and
- An appointment will be scheduled for Day 26 visit.

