#### **Visit 5 – Day 26 (+/- 1 day)**

Subjects will return to the clinic seven (7) days after Visit 4. The following assessments will be performed:

- Subject diaries will be collected and reviewed and subject will be queried regarding any adverse events they may have experienced;
- A vaginal health questionnaire will be completed;
- Five (5) vaginal samples and a vaginal pH measurement will be taken in the same manner as described for Visit 2;
- Review concomitant medications; and
- An appointment will be scheduled for Day 36 visit.

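### The straight-line time model for Shannon's index and the lactobacillus ratio does not compare probiotic with placebo and fits a 3-day course poorly

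*Protocol*

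**What the plan says.** Section 13.1.3.4 of the Protocol defines Shannon's index S and the lactobacillus ratio. Of the latter it says: "The lactobacillus ratio will be calculated for each subject at each treatment phase". The stated aim concerns linear trends and is introduced with "lactobacillus ratio trajectories differ significantly across subjects and treatment phases, the following linear mixed effect model". The model is Y_it = μ + a_i + b_i t + ε_it, described thus: "The fixed effect being the intercept only and random effects being subject intercepts and slopes". There is no fixed slope and no term for treatment, phase or period, and the unit of t (day, visit number or phase number) is not given. The section prints no other probiotic-versus-placebo comparison of these two measures. By contrast, Sections 13.1.3.1 to 13.1.3.3 say that Nugent score, pH and symptoms will be compared between the test articles.

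On dosing, the Synopsis says: "The INHP will be administered vaginally two (2) times daily for three (3) consecutive days". The two courses fall on Days 16–18 and 37–39. On sampling: "Subjects will provide vaginal samples on Days 1, 5, 15, 19, 26, 36, 40, and 47". Section 8.1 gives the spacing in the first period: "Subjects will return to the clinic four (4) days after Visit 3", and then "Subjects will return to the clinic seven (7) days after Visit 4". Section 5.3.2.2 reports that detection of the strains "declines gradually with time and that the strains cannot be detected 30 days after cessation of oral administration".

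**The concern.** A short course followed by washout should give a rise and then a fall, or a rise that is held for a while. A straight line in time summarises neither well. Section 6.2 asks whether lactobacilli become more abundant with probiotic. That is a question about level after dosing compared with before, and with placebo, not about slope.

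A slope also weights each sample by its distance from the mean sampling time. In a crossover, the same response therefore enters with different weight, or opposite sign, depending on the period in which it occurs. Microbial ecology is a named secondary objective (Section 6.1). If this model is run as printed, a null, positive or negative trend could come from the time axis and the sequence rather than from the product.

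**Working it through.** The Protocol gives no power or effect size for this analysis, so there is no figure to reproduce. The check applies least-squares slope weights, (t − t̄)/Σ(t − t̄)², at the nominal sampling days. The response, relative to pre-dose, is D at the first post-dose sample and rD one week later, and zero elsewhere. D and r are not in the Protocol; r is varied from 0 to 1.

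**One slope over the whole study (the model as printed, t in days).** Days 1, 5, 15, 19, 26, 36, 40, 47 have mean 23.625 and Σ(t − t̄)² = 1927.875. The centred values at the post-dose samples are −4.625 (Day 19), +2.375 (Day 26), +16.375 (Day 40) and +23.375 (Day 47). Fitted change over Days 1–47 is 46 × slope:

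- Probiotic first: 46 × (−4.625 + 2.375r)D/1927.875
- Probiotic second: 46 × (16.375 + 23.375r)D/1927.875

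| r | Probiotic first | Probiotic second |
|---|---|---|
| 0 | −0.11D | +0.39D |
| 0.5 | −0.08D | +0.67D |
| 1 | −0.05D | +0.95D |

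With equal numbers per sequence, the probiotic and placebo responses enter the average slope with the same total weight, so that average contains no product contrast. A difference in slopes between the two sequences would contain one, but the printed model has no sequence term.

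**Slopes fitted within a phase.** Days 15, 19, 26 (and 36, 40, 47) are 0, 4 and 11 days from pre-dose: mean 5, weights −5, −1, +6, Σ(t − t̄)² = 25 + 1 + 36 = 62. The slope is (6r − 1)D/62 per day:

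- r = 0: −D/62
- r = 1/6: zero
- r = 0.5: +2D/62
- r = 1: +5D/62

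If t is visit number, the weights are −1, 0, +1 and the first post-dose sample drops out.

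**Illustrative power.** Assumptions: 14 complete pairs, independent residuals with SD 1, two-sided 5% (the Protocol states 5% two-sided for the primary test only), non-central t with 13 degrees of freedom, no period term. Standard errors of the probiotic-minus-placebo difference:

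- Within-phase slope: √(2/(62 × 14)) = 0.0480
- Either single change from pre-dose: √(4/14) = 0.535
- Mean of both post-dose samples minus pre-dose: √(3/14) = 0.463

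For example, at D = 1.5 and r = 0.5 the slope's non-centrality is (2 × 1.5/62)/0.0480 = 1.01. For the pre-dose to 1-day change it is 1.5/0.535 = 2.81.

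| D (SD) | r | Within-phase slope | Pre to 1 day | Pre to 1 week | Mean post minus pre |
|---|---|---|---|---|---|
| 1 | 0.25 | 5% | 41% | 7% | 24% |
| 1 | 0.5 | 10% | 41% | 14% | 32% |
| 1 | 1 | 34% | 41% | 41% | 52% |
| 1.5 | 0.25 | 6% | 74% | 10% | 47% |
| 1.5 | 0.5 | 15% | 74% | 26% | 61% |
| 1.5 | 1 | 64% | 74% | 74% | 85% |
| 2 | 0.25 | 6% | 93% | 14% | 70% |
| 2 | 0.5 | 24% | 93% | 41% | 85% |
| 2 | 1 | 87% | 93% | 93% | 98% |

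For S the beneficial direction may be a fall; the argument is the same with signs changed.

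**The case against.** The strongest reply is that this is an exploratory analysis in a 14-woman pilot, that the primary McNemar test does not depend on it, and that a full analysis plan is promised and may add visit-level comparisons. That limits the severity. It does not remove the error, because the linear model is written into the Protocol.

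Several stronger readings are tempting but are not supported:

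- *The first post-dose sample always counts for nothing or against the product.* This is true of a within-phase slope over three visits. Under the whole-study slope, Day 40 has weight +16.375 and counts strongly in favour when probiotic comes second. If Phase II means only Days 36 and 40, Day 40 also counts in full.
- *Within a phase, a response fully held for a week shows a falling trend.* That requires adding Day 36 to the first phase, but Section 8.1 labels Day 36 as Treatment Phase II. On Days 15, 19 and 26 a held response gives +5D/62.
- *Reversal is the expected result.* Within a phase it needs less than 1/6 of the response left at one week. Section 5.3.2.2 describes gradual decline, and it concerns detection of the two strains, not S or the total lactobacillus ratio. The primary objective is maintenance for one week, and the follow-up allows for colonization at Days 47 and 129.
- *A larger immediate response lowers the slope.* This holds only if the Day 26 value is fixed separately. For a given r above 1/6 the slope rises with D.
- *Adding terms cannot help.* Treatment-specific slopes would keep the same weights. Indicators for post-dose level placed beside a linear time term would recover the response.

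**Conclusion.** The point stands. As printed, the model gives one slope per woman whose sign for the same response can depend on randomized sequence (−0.08D against +0.67D at r = 0.5), and it contains no term that compares probiotic with placebo. That conclusion rests on the printed model, the nominal visit days, t in days and a response back to zero before the other period.

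If the intention was a slope per phase, the fault is mainly loss of sensitivity to a transient response, with reversal confined to r below 1/6. The loss is large at r = 0.25 to 0.5 and modest if the response is fully held (64% against 74% for either single change at D = 1.5). These power figures depend on assumed D, SD, r, complete pairs and independent residuals; the slope weights do not. The consequence is for conclusions on S and the lactobacillus ratio only.

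**What to change.** In Section 13.1.3.4, replace the linear-trend model for S and the lactobacillus ratio. For each woman and product, take the change from that period's pre-dose sample (Day 15 or 36) to the 1-day sample (Day 19 or 40) and to the one-week sample (Day 26 or 47), or to the mean of the two. Compare probiotic with placebo within woman, with a period term. State that no conclusion about a product effect will rest on a linear slope in time.

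All the samples are already scheduled, so the cost is wording in the Protocol and the analysis plan. The downside is two contrasts per outcome instead of one slope. The one-week contrast alone has low power if the response fades (10% at r = 0.25 and 26% at r = 0.5, with D = 1.5), which is a reason to keep the 1-day contrast or the mean of the two beside it.

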##### **13.1.2.1 Nugent Score Analysis**

$$H_0: \pi_A = \pi_P$$

$$H_a: \pi_A \neq \pi_P$$

$\pi_A$  denotes proportion of subjects used intravaginal probiotic capsules had shown improvement in Nugent Score from intermediate (4-6) to normal status (0-3)

$\pi_P$  denotes proportion of subjects used intravaginal placebo capsules had shown improvement in Nugent Score from intermediate (4-6) to normal status (0-3)

McNemar's test will be utilized to test the hypothesis at 5% level of significance, 2-sided.

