## **13.2 Sample Size and Power Considerations**

No formal sample size calculation was performed for this study. The number of subjects to be randomized is based on feasibility and practical considerations for such an exploratory study. It is planned that a total of fourteen (14) subjects will be randomized in this study.

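### The microbiota trend model (Section 13.1.3.4) has no fixed time slope, so a trend shared by all women counts as evidence that their trends differ

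*Protocol*

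**What the plan says.** Section 13.1.3.4 derives Shannon's index (S) and the lactobacillus ratio for every woman in every phase. It then sets out to learn whether the linear trends in S and "lactobacillus ratio trajectories differ significantly across subjects and treatment phases".

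The model given for this is Y_it = mu + a_i + b_i t + e_it. The text spells out its structure: "The fixed effect being the intercept only and random effects being subject intercepts and slopes". It adds that a_i, b_i and the error "are independent normal random variables". Time appears only through b_i. There is no fixed coefficient for t and no phase or treatment term. The section names no test, null hypothesis or significance level, and it does not say whether t is a study day or a phase index.

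On the amount of data, the Synopsis says "Subjects will provide vaginal samples on Days 1, 5, 15, 19, 26, 36, 40, and 47", and Section 13.2 says "It is planned that a total of fourteen (14) subjects will be randomized in this study". Section 13.2 also states that "No formal sample size calculation was performed for this study", so no power or error-rate figure exists for this model.

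**The concern.** The across-subjects part of the aim has a clear null: all women follow the same linear trend, whatever it is. In the written model the only trend parameter is Var(b_i). Because the intercept is the sole fixed effect, b_i has mean zero. Setting Var(b_i) = 0 then says that no woman changes at all, which is a different and narrower statement than all women changing alike.

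Two things follow. A shared rise or fall can be fitted only by inflating Var(b_i), so a uniform trend may be reported as significant heterogeneity between women. And the model has no parameter for the average change, although the exploratory outcomes in Section 6.2 include whether lactobacilli become more abundant.

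**Working it through.** **Inputs from the protocol.** 14 women (Section 13.2); samples on Days 1, 5, 15, 19, 26, 36, 40 and 47 (Synopsis); the model and its fixed and random effects (Section 13.1.3.4).

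**Assumptions, because the protocol gives no figure.** Random-intercept SD = residual SD = 1. Every woman has the same slope, so the true between-woman slope variance is zero. The shared change over the whole period ranges from 0 to 2 residual SDs. The test is a likelihood-ratio test of Var(b_i) = 0 at 5%, referred to the 50:50 mixture of chi-square on 0 and 1 df. The 5% is borrowed from the primary analysis ("McNemar's test will be utilized to test the hypothesis at 5% level of significance, 2-sided").

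**Step 1, algebra.** With b_i taken as N(0, s²), s² estimates E[b²] = beta² + Var(b), where beta is the shared slope. If Var(b) = 0 and beta is not 0, s² is still positive.

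**Step 2, size by hand.** Rescale time to run from 0 to 1, so that beta is the total change in residual SDs.
- Eight visit days: days since Day 1 are 0, 4, 14, 18, 25, 35, 39, 46, with mean 181/8 = 22.625. The sum of squares about the mean is 6023 − 8 × 22.625² = 1927.9, which is 1927.9/46² = 0.911 on the rescaled axis. One woman's least-squares slope has sampling variance 1/0.911 = 1.10. A shared change of 1 SD raises the mean squared slope from 1.10 to 2.10 (1.9 times); 2 SD raises it to 5.10 (4.6 times).
- Three equally spaced phases, one value each: the sum of squares is 0.5 and the sampling variance is 2. Shared changes of 1 and 2 SD give (2 + 1)/2 = 1.5 times and (2 + 4)/2 = 3 times.

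The excess is smaller under the phase reading, so lower rejection rates are expected there.

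**Step 3, simulation, t = the eight visit days** (maximum likelihood, 600 runs per row). There is no true difference in trends in any row.

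| Shared change (residual SDs) | Model as written | Fixed slope added |
|---|---|---|
| 0 | 3.2% | 2.2% |
| 0.5 | 11.7% | 4.0% |
| 1 | 43.8% | 4.7% |
| 1.5 | 86.3% | 3.2% |
| 2 | 98.8% | 3.2% |

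Repeats with REML gave 43–47% at 1 SD and 98% or more at 2 SD for the model as written, so about 45% and 98% is a fair summary. With the fixed slope they gave 3–5%.

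**Step 4, other readings of t.**
- One value per phase, three phases: 14–18% at 1 SD and 41–46% at 2 SD.
- Three visits within one phase (Days 15, 19, 26; 400 runs): 5.8%, 16.5%, 51.5% and 89.0% for 0, 1, 2 and 3 SD, against 5–7% with a fixed slope.

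**Step 5, source of the shared change** (eight visit days).
- An identical product response that washes out appears at Visits 4–5 in one sequence and Visits 7–8 in the other. Rejection was 9%, 14%, 17% and 22% for responses of 1, 1.5, 2 and 3 SD in one set of runs, and about 10–29% over 1–3 SD in another.
- A product effect that persists: 39% at 1 SD and 98% at 2 SD.

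**Step 6, price of the fixed slope.** With real slope heterogeneity (SD 1) and no common trend, boundary-corrected power was 57% both without and with the fixed slope.

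**The case against.** The best counter-arguments concern size and scope.

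- **The test is not the protocol's.** Section 13.1.3.4 names none, and Section 13.1 promises a full statistical analysis plan. This stands as a limit on the rejection rates: they describe one reasonable test, not a planned one. It does not remove the defect, because the protocol itself fixes the equation and excludes a fixed slope, and any test resting on Var(b_i) inherits the wrong null.
- **The mean of b_i is never said to be zero.** True, but a non-zero mean would be a fixed slope, which the sentence on fixed effects rules out.
- **The time scale is open.** This stands. The section computes its measures by phase, and under a three-phase reading the inflation is much smaller.
- **A reader might infer that a uniform response to the probiotic would be declared heterogeneity.** The documents do not support that in general. Order is randomized, dosing lasts three days, and an 18-day washout follows (Section 6), so a response that fades is not one line shared by both sequences and inflates the rate only modestly. The high rates need a drift common to all women or an effect that persists. Persistence cannot be dismissed, since the protocol follows women still colonized at Day 47, but it is not established either.
- **The missing phase and treatment terms are the larger gap.** Fair. Adding a fixed slope does not fill that gap.

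**Conclusion.** The point holds in this form: the model as written cannot separate a trend shared by all women from trends that differ between them, and it does not estimate the average trend. That conclusion is algebraic and needs no assumed figure.

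The size does depend on assumptions: unit SDs, a 5% boundary-corrected likelihood-ratio test and the meaning of t. On those terms, false rejection at shared changes of 1 and 2 residual SDs is about 45% and 98% on the eight visit days, or about 14–18% and 41–46% over three phases. With no shared trend the rate is nominal. The protocol gives no basis for saying how large a common drift would be.

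It would be wrong to infer that the trial's main conclusion is at risk. This is an exploratory analysis in a pilot sized on feasibility, and the primary McNemar comparison does not use this model. The correction is still worth making, because the error is written into the protocol and costs almost nothing to remove.

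**What to change.** In Section 13.1.3.4, change the sentence on fixed effects so that they are the intercept and linear time, and write the model as Y_it = mu + beta t + a_i + b_i t + e_it. Report beta with its 95% confidence interval as the average trend. Test Var(b_i) = 0 around it against the 50:50 chi-square mixture, name that test and its level, and state what t measures.

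This repairs only the across-subjects part of the aim. To address the across-phases part, add phase or treatment terms, with their interactions with time, in the same revision. Until then beta is a calendar-time slope pooled over untreated, placebo and probiotic periods and should be described as such.

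The fixed slope costs one parameter and one changed sentence. It needs no further women, visits or samples, and the simulation showed no loss of power.

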## **6 STUDY DESIGN**

The study population will consist of post-menopausal subjects presenting with intermediate Nugent Scores (4-6). The study duration is 47 days with a final follow-up at 129 days. A total of fourteen (14) subjects will be randomized into this exploratory study.

Subjects will undergo the following treatment phases:

- Two weeks of no treatment (Days 1-15); followed by
- Three days in which each subject randomly receives either two intravaginal placebo capsules or two intravaginal probiotic capsules (Days 16-18) each day; followed by
- 18 day wash-out period; followed by
- Three days in which each subject randomly receives either two intravaginal placebo capsules or two intravaginal probiotic capsules (Days 37-39) each day; and
- Follow-up approximately 90 days after last treatment.

The capsules given on Days 37-39 will not be the same as the capsules given on Days 16-18. During one treatment period the probiotic will be given and during the other treatment period, placebo will be given. Not the subject nor the study staff will know which capsules contain the probiotics.

INHP (placebo or probiotic) consists of capsules to be administered vaginally on study treatment days; once in the morning and once in the evening approximately 12 hours apart.

Following the first two weeks of no treatment, subjects will be given six (6) placebo or probiotic capsules, on Day 15, to be administered vaginally twice daily for 3 consecutive days. Panty liners will be given to use on treatment days. On Day 36, subjects will again be given six (6) placebo or probiotic treatment capsules to be administered vaginally twice daily for

3 consecutive days in the same manner. A diary to track compliance and to rate general vaginal discomfort and record any other adverse events will be given to the patients and reviewed by the study Investigator or designee at the following visit. Subjects that remain colonized with the probiotic strains at Day 47 will return for a follow-up visit on Day 129. During the follow-up phase, all subjects who received treatment will be queried monthly via telephone regarding adverse events on a monthly basis until Day 129. See Section 8 for visit details.

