### **Secondary Objectives:**

Determine the effect of *L. rhamnosus* GR-1® and *L. reuteri* RC-14® on the subjects' anti-microbial defences and vaginal comfort as measured by:

- Microbial ecology analysis, human genetic microarrays and multiplex immunological assessments; and
- An increase in symptom relief such as itching, irritation, or general vaginal discomfort.

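### The diversity–symptom regression can take up to four rows from one woman with no subject term, so its slope test is generally not at its nominal level

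*Protocol*

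**What the plan says.** Protocol Section 13.1.3.4 begins this analysis with "In order to determine if a statistical relationship existed between microbial diversity and vaginal symptoms, a weighted least squares analysis". It then writes the model out as Ȳ_id = μ0 + μ1·d + ε_id, where Ȳ_id is the mean Shannon index of subject i at symptom level d. The model "will be used to test the linear effect of vaginal symptoms with respect to microbial diversity". On the regressor it says: "Severity of vaginal symptoms will be treated as ordinal values 0, 1, 2, and 3, for example". The legend to the equation, however, calls d dryness.

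Four other statements bear on the point:

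- **Size and sampling.** Section 6: "A total of fourteen (14) subjects will be randomized into this exploratory study". Synopsis: "Subjects will provide vaginal samples on Days 1, 5, 15, 19, 26, 36, 40, and 47".
- **Values per woman.** Section 13.1.3.4 also says the index is computed per subject and treatment phase, so it is unclear whether a woman has eight index values or about three.
- **Neighbouring model.** The mixed model for the trend in the index, in the same section, gives each subject her own intercept and slope.
- **Symptoms and OTUs.** Section 13.1.3 names "symptoms such as itching, irritation, and general vaginal discomfort", with others allowed. The Shannon sum runs to 119, with no source for that number.

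**The concern.** The double index means one row per woman per severity level. A woman whose symptoms change over the study therefore enters several times, and her rows share whatever makes her diversity generally high or low. An intercept-slope-error fit with simple weights takes those rows as unrelated. Its standard error then does not describe how the slope actually varies, and its p-value is not what it claims to be.

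This is more than a detail left open: the protocol fixes the equation and says it will be used for a test, while the adjacent model does carry subject effects. Microbial ecology and symptom relief both appear among the secondary objectives (Section 6.1: "An increase in symptom relief such as itching, irritation, or general vaginal discomfort"), and this regression is the only stated analysis that links them.

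**Working it through.** The protocol states no error rate or power for this analysis, so there is no figure to reproduce.

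**Inputs from the protocol.** 14 women, up to 8 sampling days and 4 severity levels. That is at most 14 × 8 = 112 index values and 14 × 4 = 56 rows.

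**Assumptions, not in the protocol.** Two-sided 5% (stated only for the McNemar test); weights equal to the number of values behind each mean; index with total SD 1 and within-woman correlation 0 to 0.7; a latent normal severity with within-woman correlation 0 to 0.9, cut at −0.25, 0.55 and 1.3 to give 0–3.

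**Why the direction is not fixed.** Let the index have between-woman variance τ² and within-woman variance σ². Let Sxx be the weighted sum of squares of severity, B the share of Sxx lying between women, and R the number of rows. With eight values per woman:

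- true variance of the slope = (σ² + 8·B·τ²) / Sxx
- variance reported by the fit ≈ (σ² + (112/R)·τ²) / Sxx

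The two agree if τ² = 0 or if B = 14/R. The simulated average R was 46 when severity varied freely within women, so the crossover is 14/46 = 0.30. At severity correlation 0.9, R was 25 and the crossover 14/25 = 0.56. Below the crossover the test is conservative; above it, liberal.

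Example: τ² = 0.7, σ² = 0.3, no severity correlation, so B is about 1/8 by chance.

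- Reported: 0.3 + 0.7 × 112/46 = 2.00
- True: 0.3 + 0.7 × 8 × 1/8 = 1.00

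The reported variance is twice the true one. The effective cut-off is 1.96 × √2 = 2.77, a rejection rate of about 0.6%. The simulation gave 0.4%.

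**Type I error of the stated model, nominal 5%, 3,000 runs per cell (simulation error about √(0.05 × 0.95/3000) = 0.4 points).**

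| Index correlation | Severity corr. 0 | 0.3 | 0.5 | 0.7 | 0.9 |
|---|---|---|---|---|---|
| 0 | 5.6% | 5.6% | 5.8% | 5.1% | 4.5% |
| 0.3 | 2.3% | 5.6% | 7.3% | 8.1% | 9.0% |
| 0.5 | 1.4% | 4.9% | 8.3% | 10.9% | 10.5% |
| 0.7 | 0.4% | 4.6% | 8.6% | 11.0% | 11.5% |

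The first row shows that the clustering is the cause. Adding a fixed intercept per woman to the same weighted rows gave 3.8% to 5.8% in every cell. With equal weights and index correlation 0.3 to 0.7, the stated model ran from 0.2% to 7.8%. A second simulation of the eight-value layout, under its own assumptions, gave about 3% to 13% for the stated model and about 4% to 6% with a subject intercept.

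**Power for a slope of 0.3 SD per level, 1,500 runs.**

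| Index / severity correlation | Stated model | Fixed subject intercept |
|---|---|---|
| 0.7 / 0 | 65.4% | 99.8% |
| 0.5 / 0.5 | 58.3% | 82.5% |
| 0.3 / 0.9 | 53.7% | 27.3% |

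In the last line the stated model's own type I error is 9.0%.

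**Three values per woman (phase-level index).** Type I error of the stated model was 3.4% to 9.4%. For a slope of 0.2 SD and index correlation 0.3 to 0.5, power was 21% to 25% for the stated model and 10% to 29% with a fixed subject intercept. At index correlation 0.85 it was 22% to 24% against 35% to 74%.

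**The 119 limit.** Unused terms add zero, so with fewer OTUs the index is exact. In one example each with 150 and 200 OTUs, keeping the 119 most abundant changed the index by less than 0.001 (3.2724 against 3.2722 for 200).

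**The case against.** The best defence is that independence of the errors is stated only for the neighbouring mixed model. Weights and error covariance for this regression may be set in the SAP, and a weight matrix carrying within-woman covariance would cure the problem. That is fair, but nothing in the protocol points to such a matrix, and the equation as written has no subject term.

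It is also true that eight values per woman is a maximum. Section 8.1 stops some women at Visit 3 or Visit 6, and the phase-level wording may mean about three values. With three, the departure from 5% is smaller and the power gain from a fixed subject intercept mostly disappears. All the correlations are assumed.

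A reader might infer more than the documents support:

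- **That the test always overstates significance.** It can be conservative, near nominal or liberal.
- **That dryness or the figure 119 makes the error rates wrong.** Neither enters them. The symptom lists are open-ended and the vaginal health questionnaire is not shown, so dryness may well be collected.
- **That any OTU count other than 119 gives a wrong index.** A smaller count leaves it exact.
- **That within-woman information is lost.** Contrasts between levels within a woman still enter the fit; they are used inefficiently.

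**Conclusion.** The point holds for the missing subject term. As written, the slope test is generally not at its nominal level, and the sponsor cannot tell beforehand in which direction it errs. At nominal 5%, type I error runs from below 1% to about 13% with eight values per woman and from about 4% to 9% with three. It is near nominal where the index has no within-woman correlation or severity is only moderately clustered.

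These sizes rest on assumed correlations, weights and severity cut-points. The missing subject term itself rests on the protocol's equation alone. The consequence is limited to one exploratory association in a 14-woman pilot; the primary McNemar test and the safety analyses are untouched.

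**What to change.** Replace the weighted least squares model with a mixed model with a random subject intercept, for example:

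> For each analysed symptom, the Shannon index of subject i at visit t will be modelled as S_it = μ0 + μ1·d_it + a_i + ε_it, with a_i a random subject intercept. The slope μ1 will be tested with degrees of freedom suited to 14 subjects.

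State whether the index is computed per visit or per phase, and use visit level if it is available. If the stated rows are kept, define the weights and use a subject-clustered variance suited to 14 clusters. The weights matter: with equal weights on the averaged rows, even a fixed subject intercept gave 5.4% to 8.3%.

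A random intercept is preferable to the fixed one simulated above because it also uses differences between women, on the assumption that one slope holds within and between them. It was not itself part of the tabulated run.

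Three minor wording corrections, none affecting error rates: name the symptoms actually analysed in place of dryness; sum the Shannon index over all observed OTUs; and call μ1, not μ1·d, the slope.

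The cost is analysis wording only, with no added visit or sample. The downside is lower apparent power when symptoms hardly vary within a woman; there, the stated model's higher power comes with an inflated error rate.
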